**Fig. 3 Fig3:**
[figure not shown]
*Left*: activation map constructed during sinus rhythm. The atrial complexes (*A*) of all 192 recordings are automatically detected and marked at the steepest deflection. The electrode with the earliest atrial marking is set at time (*T*) 0. Activation times of the other electrodes are in reference to T_0_. Isochrones are set at 5 ms intervals after T_0_. The *black/white arrow* illustrates the direction of conduction. Conduction block (<18 cm/s) is represented by *thick black lines. V* ventricular complex. *Right*: The mapping surface is divided into quadrants and parameters such as block %, and mean voltage are determined for each quadrant of each mapping location (total: 36 quadrants). *LA* left atrium, *PV* pulmonary veins, *BB* Bachmann’s bundle, *RA* right atrium

**Fig. 4 Fig4:**
[figure not shown]
*Left*: wave map during atrial fibrillation at the right atrial free wall. A total of 5 waves activate the recording area in 41 ms; 3 peripheral waves (*black arrows*) and 2 initiate at epicardial breakthroughs (*white star and white arrows*). *Black lines* between electrodes indicate conduction block (<18 cm/s). Isochrones of waves are set at steps of 5 ms after T_0_. Parameters derived from the wavemap include a number of epicardial breakthroughs, waves, and conduction velocity. *Right*: Examples of corresponding electrograms are shown. The parameters that will be derived from electrograms include atrial fibrillation cycle length (AFCL), fractionation, and voltage

The present study is the first that will explore the value of various parameters in discriminating the arrhythmogenic substrate of different patients with AF. We aim for a sample of (at least) 50 subjects in each group for the following reasons. First, our initiative should be considered as an exploratory study. We want to obtain early results in a relative limited number of patients, which will provide a basis for future (in depth) investigations. Therefore, we accept that our study will be underpowered to draw definite conclusions with good precision. Additionally, it is relevant to obtain estimates with sufficient precision, also in early, hypothesis generating studies such as ours. In the binomial distribution, a probability of an observation of 50 % is achieved with the greatest measurement error. Taking that probability as the ‘worst case’, in a dataset of 50 patients, the 95 % confidence intervals (CIs) around an observation would be ±14 %. In the 6*50 = 300 AF patients together, the 95 % CIs would be ±6 %. We consider these precisions acceptable for this exploratory study that will, hopefully, discover parameters that may be used in future studies to discriminate between AF patients with different underlying heart diseases.

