**Fig. 1 Fig1:**
[figure not shown]
Flow-chart of patient inclusion and following study procedures. After enrollment, patients are assigned to 1 of 12 groups for data analysis according to the presence of previous atrial fibrillation (*AF*) occurrence and the type of surgery that will be performed (i.e., underlying heart disease). Subsequently, all patients are mapped during surgery and continuously monitored after surgery to detect postoperative AF. During the 5-year follow-up (*FU*), the additional tests consist of an electrocardiogram (*ECG*) and Holter monitoring when patients indicate symptoms suspected of AF. *ICF* informed consent form, *CABG* coronary artery bypass grafting, *MV* mitral valve surgery, *AV* aortic valve surgery, *CHD* congenital heart disease

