### Data and Statistical Analysis

Local activation times of the recorded atrial signals will be marked, from which color-coded activation and wave maps will be reconstructed by custom-made software which has previously been described in more detail [11]. Data exclusion criteria include progressive in- or decrease in AF cycle length (AFCL) between sequential recordings (recorded via the reference signal) indicated by an approximately two times in- or decrease in AFCL, recordings of other rhythms than sinus rhythm or AF, or ≥50 % of missing recording data. Data analysis and the criteria for data inclusion are demonstrated in Fig. 2. Electrophysiological parameters that will be derived include conduction velocity, incidence of conduction block, number of fibrillation waves, incidence of epicardial breakthroughs, AFCL, dominant frequency, electrogram voltage (the amplitude of the highest deflection in case of fractionation) and fractionation [11, 12]. For analysis, the electrodes of the mapping array are assigned to quadrants of 1 cm^2^. The variables will consist of averaged values or the percentage of occurrence/incidence for each quadrant. Figure 3 illustrates the construction of an activation map during sinus rhythm, quadrant partition, and its conversion into various parameters of all atrial sites. Figure 4 shows a wave map during AF and the variables that will be analyzed. Furthermore, rotor occurrence and the relation between patterns of activation, fractionation, fibrillation intervals, conduction abnormalities, and voltage will be studied and compared between the different atrial sites, atrial rhythms, and patient groups. Rotors will be defined as a wave of excitation rotating around a phase singularity for one or more cycles [15] and analyzed by determining the dominant frequencies at each recording site in order to identify high-to-low frequency gradients and determination of the degree of linking of fibrillation waves, indicative of repetitive patterns of activation. Linear regression analysis and paired Student’s *t* test will be used to compare various electrophysiological parameters between different sites and different atrial rhythms. Unpaired Student’s *t* test will be used to compare various electrophysiological parameters between patient groups.

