### Clinical Relevance

This project can provide the tools to discriminate the arrhythmogenic substrate of AF in patients with different heart diseases and is potentially the first step towards a patient-tailored strategy for the treatment of AF.

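### The stated aim is discrimination between AF patients, but the only named test between patient groups is the unpaired t test, which does not measure discrimination

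*Protocol article*

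**What the plan says.** The aim appears in the sample-size paragraph that closes Data and Statistical Analysis (after the Fig. 4 legend): the study is the first to "explore the value of various parameters in discriminating the arrhythmogenic substrate of different patients with AF". The same paragraph ends with the hope that it will "discover parameters that may be used in future studies to discriminate between AF patients with different underlying heart diseases". The Clinical Relevance section goes further: "This project can provide the tools to discriminate the arrhythmogenic substrate of AF in patients with different heart diseases".

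The inferential methods are in Data and Statistical Analysis. Between sites and rhythms, linear regression and a paired Student's t "test will be used to compare various electrophysiological parameters between different sites and different atrial rhythms". Between groups, an unpaired Student's t "test will be used to compare various electrophysiological parameters between patient groups". No AUC, sensitivity or specificity, classification measure or effect-size criterion is mentioned.

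On size, the Fig. 1 legend says that "patients are assigned to 1 of 12 groups for data analysis", and the sample-size paragraph says: "We aim for a sample of (at least) 50 subjects in each group for the following reasons". The precision argument given there concerns the confidence interval of a single proportion.

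**The concern.** A test of means and a measure of discrimination answer different questions. The t test asks whether two averages differ by more than chance would explain. Discrimination asks how far the two distributions overlap, and so how often a patient's value points to the right group. Two groups can differ significantly on average while most of their values overlap.

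The results are meant to inform which parameters later studies use. If a significant t test is the only between-group result reported, a reader may take a parameter to be discriminating when it classifies patients only a little better than chance. The sample-size argument does not fill the gap, because the precision of one proportion is neither the precision of a mean difference nor that of a discrimination measure.

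**Working it through.** **Inputs from the article:** at least 50 patients per group; 12 groups (six surgery types, each with and without prior AF); unpaired t test between groups.

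**Assumptions (not in the article):** two-sided alpha 0.05; one normally distributed value per patient; equal SDs in the two groups.

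**1. The article's own precision figures.** Half-width = 1.96 × √(0.25/n).
- n = 50: 1.96 × √(0.25/50) = 0.139, stated as ±14%.
- n = 300: 1.96 × √(0.25/300) = 0.057, stated as ±6%.

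Both reproduce and are not in dispute.

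**2. Smallest difference that is significant at 50 v 50.** d = t(0.975; 98 df) × √(1/50 + 1/50) = 1.984 × 0.200 = 0.397 SD.

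**3. What that difference means for separating patients.**
- AUC = Φ(d/√2) = Φ(0.281) = 0.611.
- Correct at the best cut-off = Φ(d/2) = Φ(0.198) = 0.579, against 0.50 by chance.
- Sensitivity at 80% specificity = 1 − Φ(0.842 − 0.397) = 0.328.
- Overlap of the two distributions = 2 × Φ(−d/2) = 0.843.

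**4. Stronger results, for scale.**
- The difference detectable with 80% power at 50 v 50 is 0.566 SD: AUC 0.655, 61% correct.
- AUC 0.80 needs √2 × Φ⁻¹(0.80) = 1.19 SD, about three times the significance threshold (1.19/0.397 = 3.0).

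**5. Precision if the AUC is estimated instead (Hanley–McNeil, 50 v 50).** SE² = [A(1 − A) + 49(Q1 − A²) + 49(Q2 − A²)]/2500, with Q1 = A/(2 − A) and Q2 = 2A²/(1 + A). For A = 0.61:
- Q1 = 0.4388, Q2 = 0.4622, A² = 0.3721.
- SE² = (0.238 + 3.271 + 4.417)/2500 = 0.00317, so SE = 0.0563.
- Half-width = 1.96 × 0.0563 = 0.110.

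| AUC | 95% CI half-width, 50 v 50 |
|---|---|
| 0.61 | 0.110 |
| 0.70 | 0.102 |
| 0.80 | 0.087 |

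The planned groups therefore support an exploratory AUC without further recruitment.

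**The case against.** The other side has a good case, and several parts of it stand.

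- **Selection by p-value.** A reader might infer that parameters will be picked by significance. The article gives no alpha, threshold or ranking rule, and it justifies its sample by interval width, which is an estimation argument.
- **Large pooled comparisons.** A reader might infer a comparison of 300 v 300, in which very small differences would pass. The article uses 300 only for the interval around one proportion in all AF patients together. For contrasts between disease groups among AF patients, 300 v 300 cannot arise, because those 300 are spread over six groups.
- **Significant means useless.** A reader might infer that any significant parameter discriminates poorly. AUC 0.61 holds only at the bare threshold; larger observed differences give larger AUCs.
- **Failure of the study.** A reader might infer that the study cannot meet its purpose. It is declared exploratory and underpowered, the Introduction also aims at knowledge of pathophysiology, and use of the parameters is referred to later work: "parameters that may be used in future studies to discriminate between AF patients with different underlying heart diseases". Comparing means is a reasonable first step for that.
- **Ranking.** With equal group sizes, normal data and equal SDs, AUC and p-value put parameters in the same order, so the AUC would not change the ranking there.
- **Omission.** A full protocol or SAP, not shown, may add discrimination measures.

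The last two points do not dispose of the matter. Even when the order is the same, a p-value does not tell the reader whether the leading parameter separates patients well. The AUC also remains interpretable for skewed parameters, such as percentages of conduction block per quadrant, and for unequal groups, which a minimum of 50 per group allows. And the point does not rest on a missing detail: the article states both the aim and the between-group test, and the two do not match.

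**Conclusion.** The point stands in a limited form. The article sets out to explore discriminating value and names, for patient groups, only a test of means. At 50 v 50 the weakest significant result corresponds to about 0.40 SD, AUC about 0.61 and 58% correct at the best cut-off, so significance alone does not establish useful discrimination. These figures assume alpha 0.05, normal data, equal SDs and one value per patient, none of which the article specifies. The t test is not wrong for comparing means, and the article's precision figures are correct. The change should be made, but the study remains informative without it.

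**What to change.** In Data and Statistical Analysis, keep the t tests as supporting analyses and add the following:

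1. Summarise each parameter to one value per patient. The variables are defined per quadrant and Fig. 3 gives 36 quadrants, so quadrants must not be counted as separate patients.
2. For each parameter, report the AUC with 95% CI for the comparisons between disease groups among AF patients and, secondarily, for AF v no AF within each surgical group.
3. Base any statement that a parameter discriminates on the AUC and its CI, not on t-test significance.

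**Cost.** A modest amount of extra analysis on data already being collected, with no additional patients or recordings. If all pairs of the six disease groups are compared, there are 6 × 5/2 = 15 AUCs per parameter, which should be presented as exploratory. Results will look less favourable: a parameter at AUC 0.61 would carry a 95% CI of roughly 0.50 to 0.72 (0.61 ± 0.11), and one at 0.80 roughly 0.71 to 0.89 (0.80 ± 0.09).

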### Ethics

The study protocol was approved in February 2010 by the Medical Ethics Committee (2010–054) in the Erasmus Medical Center, Rotterdam, The Netherlands.

## Discussion

### Study Population and Mapping Sites

Previous epicardial mapping studies for AF were performed in small numbers of patients and at only a few atrial sites or with a low resolution [11, 12, 16–19]. The present study is the first to perform intra-operative high-resolution *epicardial mapping* in a large number of patients and enables analyses between patients with different heart diseases. In addition, all sites of both the right and the left atrium accessible from the epicardial side are mapped including Bachmann’s bundle. Bachmann’s bundle might have an important role in the pathophysiology of AF [20]. By mapping the entire surface of both atria there is an increased chance of finding the arrhythmogenic substrate, which might be located in different atrial regions among AF patients.

### The Arrhythmogenic Substrate in AF

The heterogeneous nature in which AF presents and the frequently failing AF treatments so far, demonstrate the importance for an individualized strategy in the treatment of AF. The first step is a better understanding of the pathophysiology underlying initiation and perpetuation of AF. The focus for initiation of AF often originates in the pulmonary veins and Moe et al. described the concept of self-sustaining fibrillatory waves responsible for perpetuation of AF [21, 22]. However, recurrences of persistent AF after successful isolation of the pulmonary veins cannot be explained by these concepts alone. The occurrence of longitudinal dissociation during AF was demonstrated later on and showed to be most prominent in persistent AF [11]. Furthermore, focal fibrillation waves emerging within the recording area, referred to as epicardial breakthroughs, occur much more frequently during persistent AF than during acute AF [12], as well as drivers such as rotors and focal sources [23]. These findings suggest that progressive electro-pathological changes within the atria are associated with persistent AF. Nonetheless, the exact pathophysiological changes and locations at which they occur are not yet known. The underlying diseases most likely initiate different pathophysiological mechanisms that lead to AF. For example, valvular disorders give rise to atrial pressure or volume overload, coronary artery disease can cause atrial ischemia and infarction, and congenital heart diseases may also include congenital atrial abnormalities. For this reason, the patients in this study are divided in separate groups according to the underlying heart disorders and AF occurrence prior to surgery.

Previous studies have investigated the underlying cause responsible for perpetuation of AF. Atrial fibrosis has been suggested to be an important element in the pathophysiology of AF. There is a significant larger amount of atrial fibrosis seen in patients with AF [7, 24]. An excessive extracellular matrix leads to uncoupling of cells and may facilitate inhomogeneous conduction, re-entry, and multiple wavelets. MRI or electro-anatomical voltage mapping can be helpful diagnostic tools for the determination of degree of fibrosis in AF patients and identification of areas of fibrosis. However, no association has been found between the amount of fibrosis and clinical AF characteristics [7, 24]. Electrical signal conduction involves processes on a structural, cellular and molecular level, and these together determine if conduction is altered and AF occurs. Therefore, the arrhythmogenic substrate can probably be more accurately localized by measuring electrical potentials and conduction. In the present study, both the recorded extracellular potentials and the spatial domain of the electrograms enables conversion into specific electrophysiological parameters that could identify areas with conduction abnormalities. If proven successful, this strategy can be developed into a diagnostic tool for each individual AF patient. In addition, current ablation strategies aimed at identifying and targeting arrhythmogenic areas are not effective in a large proportion of patients and might even lead to new arrhythmias [25]. If patients that can benefit could be selected beforehand, effectiveness of these treatments might improve.

### Study Limitations

Currently, epicardial mapping can only be performed during open-chest cardiac surgery. Therefore, it is not possible to perform epicardial mapping in patients with nondiseased hearts. However, with constantly advancing techniques it may become possible in the future to perform epicardial mappings during video-assisted thoracoscopic surgery in patients without any heart disease. Secondly, although epicardial mapping can reach sites endocardial mapping cannot, some sites are not accessible, for example, the atrial septum. Therefore, epicardial mapping is not able to analyze conduction in the entire area of the atria. In addition, recordings are performed sequentially, as simultaneous high-resolution mapping of the entire surface is not possible yet with currently available technical equipment. As time during surgery is limited, mapping is performed immediately after AF induction or electrical conversion. Consequently, if a progressive increase, or decrease in AFCL occurs during the recordings, this data will have to be excluded [26–28]. General anesthesia may also increase AFCL [29]. However, the same anesthetic protocol is applied in all patients and previous studies have shown that there remain differences in AF between patients despite anesthesia [11, 12]. Furthermore, recent studies have shown that endo-epicardial dissociation can occur during AF and might be associated with persistent AF [30]. This suggests that it is important to investigate endocardial and epicardial conduction simultaneously as conduction can be disturbed in all three dimensions. Finally, there is a small chance asymptomatic persistent AF episodes may be undetected during follow-up. The measured incidence of persistent late postoperative AF may therefore underestimate the true incidence of persistent late postoperative AF.

### Clinical Relevance

This project can provide the tools to discriminate the arrhythmogenic substrate of AF in patients with different heart diseases and is potentially the first step towards a patient-tailored strategy for the treatment of AF.

### Project Status

At present, the inclusion for this study is ongoing. We expect the data of this project to become available in 2016 or 2017.

## Abbreviations

AF: Atrial fibrillation
CABG: Coronary artery bypass grafting
ECG: Electrocardiogram
AFCL: Atrial fibrillation cycle length
